##### Outcome 3: All-cause and cause-specific mortality

We will define all-cause and cause-specific mortality using the linked ONS mortality data set. These include the date of death and cause of death using ICD-9 codes. We will investigate three specific causes of mortality: (1) diseases of respiratory system (ICD-10=J00-J99), (2) cardiovascular disease (ICD-10=I00-I52), and (3) anxiety and depression (ICD-10=F31.3, F31.4, F31.5, F32, F40-F48). We will use validated code lists for each outcome.

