**Methods:**

In this project we will investigate the effects of varenicline compared to nicotine replacement therapies on: (1) long-term smoking cessation and whether these effects differ by area level deprivation; and (2) the following clinically-important outcomes: rate of general practice and hospital attendance; all-cause mortality and death due to diseases of the respiratory system and cardiovascular disease; and a primary care diagnosis of respiratory illness, myocardial infarction or depression and anxiety. The study is based on a cohort of patients prescribed these smoking cessation medications from the Clinical Practice Research Datalink (CPRD). We will use three methods to overcome confounding: multivariable adjusted Cox regression, propensity score matched Cox regression, and instrumental variable regression. The total expected sample size for analysis will be at least 180 000. Follow-up will end with the earliest of either an ‘event’ or censoring due to the end of registration or death.

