### Study aims

What is the effect of varenicline on smoking abstinence? We will investigate the effects of varenicline on smoking abstinence because existing evidence from RCTs typically only followed participants for 1 year, and are not informative about long-term outcomes.What are the effects of varenicline on NHS service use? We will investigate the effects of varenicline prescriptions on all-cause primary and secondary care utilisation because smoking increases morbidity and imposes major costs on the healthcare services.^16^What are the effects of varenicline on all-cause and cause-specific mortality? We will investigate the incidence illnesses in the Clinical Practice Research Database (CPRD) using primary care diagnoses, admission to secondary care using ICD-10 codes, and Office of National Statistics (ONS) mortality records to maximise the number of events detected.What are the effects of varenicline on common physical and mental health conditions? We will investigate the effects of varenicline on rates of cardiovascular outcomes and respiratory illnesses, as previous research has suggested that patients prescribed varenicline may have different rates of these outcomes.^9^
^10^ Second, we will investigate the effects of varenicline on rates of depression and anxiety because there has been some reports that varenicline may reduce the risk of these outcomes.^13^We will also examine differences in smoking cessation medication effectiveness by socioeconomic position. A recent systematic review reported that stop-smoking services may be helping to reduce inequalities in smoking prevalence by preferentially targeting smokers of lower socioeconomic position (SEP). Data from primary care records The Health Improvement Network (THIN) show that between 2008 and 2010, smokers in more deprived groups were more likely to receive smoking cessation interventions.^17^

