##### Outcome 2: Frequency of GP and hospital attendance

We will define service use as the number of visits to GP and hospitals in the 3, 6, 9, 12, 24 and 48 months after first prescription. We will define GP appointments using the clinical data file of the CPRD. This includes all the diagnoses and symptoms that GPs record about all of their patients. As with the other outcomes, the vast majority of diagnoses and symptoms include the date on which the data were added to the database. We will use these dates to calculate the number of times each patient attends primary care. We will define the hospital visits outcome using the linked HES data. We will investigate all-cause hospitalisation and three specific causes of hospitalisation: (1) diseases of respiratory system (ICD-10=J00-J99), (2) cardiovascular disease (ICD-10=I00-I52) and (3) anxiety and depression (ICD-10=F31.3, F31.4, F31.5, F32, F40-F48). Causes of hospitalisation are available for approximately half of the sample. Again these data contain the date on which the event occurred, which we will use to define attendance to secondary care within 3, 6, 9, 12, 24 and 48 months after first prescription.

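### The anxiety and depression code list omits recurrent depressive disorder (F33), and the death data are described as ICD-9 while every cause is defined in ICD-10

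*Protocol article*

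**What the plan says.** Outcome 2 (Frequency of GP and hospital attendance) splits hospital admissions from the linked hospital data into three causes, each fixed by ICD-10 codes. The third reads "3) anxiety and depression (ICD-10=F31.3, F31.4, F31.5, F32, F40-F48). Causes of hospitalisation are available for approximately half of the sample".

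Outcome 3 (All-cause and cause-specific mortality) describes the linked national death records thus: "These include the date of death and cause of death using ICD-9 codes". The following sentence begins "We will investigate three specific causes of mortality: (1) diseases of respiratory system (ICD-10=J00-J99", continues with I00-I52 for cardiovascular disease, and ends "and (3) anxiety and depression (ICD-10=F31.3, F31.4, F31.5, F32, F40-F48". The section closes with a general assurance: "We will use validated code lists for each outcome".

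The Study aims mention the two linked sources together: "admission to secondary care using ICD-10 codes, and Office of National Statistics (ONS) mortality records". There the ICD version is attached to admissions, and the death records are named without one.

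**The concern.** Two things in these sections do not fit together.

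First, a category labelled anxiety and depression would be expected to contain recurrent depression. The printed list includes depressive phases of bipolar disorder and single depressive episodes but not the recurrent form, and gives no reason. Because the same list serves admissions and deaths, the gap affects both outcomes. The patients concerned have, by definition, had depression more than once. The plan itself treats psychiatric history as relevant to the comparison, since previous psychiatric illness is among the listed confounders.

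Second, the section on mortality names one ICD version for the data and another for the definitions. A programmer working from this text cannot tell whether the lists can be run directly on the death records or must first be translated.

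**Working it through.** No sample size or power figure is involved, so the check is a reading of the code lists against their labels and data source.

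**Step 1. Which depression codes does the printed list hold?** The list is F31.3, F31.4, F31.5, F32 and F40-F48. Testing codes for membership gives:

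| Code | Meaning in ICD-10 | In the list? |
|---|---|---|
| F31.3 | bipolar disorder, depressive episode | yes |
| F32 | single depressive episode | yes |
| F33 | recurrent depressive disorder | no |
| F33.2 | subcategory of F33 | no |
| F41 | anxiety disorders | yes |

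The absence of F33 is visible in the text; its meaning comes from the ICD-10 classification itself. The lists under Outcome 2 and Outcome 3 are identical, so the result holds for admissions and deaths alike.

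**Step 2. What follows for the analysis?** Outcome 2 counts visits within fixed windows after first prescription, and the Cox models use the first event.

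- A patient whose only relevant records are F33 is a non-event in every analysis of this cause.
- A patient with an F33 record and a listed record is still captured as having an event, but the F33 admission is missing from the count. If it came first, the event date is later than it should be.
- A death attributed only to F33 is not counted in the third cause of death, though it still counts in all-cause mortality.

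Let s be the share of intended events that are missed. If s is the same in both treatment groups and the outcome is rare, the hazard ratio is roughly unchanged but precision falls, and the risk difference from the instrumental variable analysis shrinks by the factor 1 - s. If s differs between groups, the hazard ratio is multiplied by about (1 - s for varenicline)/(1 - s for nicotine replacement). The article gives neither share.

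**Step 3. Can the loss be sized?** The Power calculations section reports 213 patients with admissions for depression or anxiety within 2 years, against 1374 for respiratory and 1022 for cardiovascular disease. By patients it is the rarest of the three, so lost cases matter most here. But the 213 is given without a code list or a breakdown by code. It may or may not already include F33, and s cannot be derived from it.

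**Step 4. ICD version of the death data.** Side by side:

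| Place | Data | ICD version |
|---|---|---|
| Study aims | admissions | ICD-10 |
| Study aims | death records | not stated |
| Outcome 2 | admissions | ICD-10 |
| Outcome 3, description of data | deaths | ICD-9 |
| Outcome 3, definitions of the three causes | deaths | ICD-10 |

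Admissions are consistent throughout. For deaths, adjacent sentences disagree, no mapping is given, and no other section resolves it.

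**The case against.** **The version conflict is editorial.** All three causes are explicitly labelled ICD-10 and repeat the lists used for admissions, so the intended definitions are clear and ICD-9 is most plausibly a slip. This largely stands. A reader might infer that the rule, taken literally, would pick out no deaths at all. That treats a descriptive sentence as the selection rule, and the text does not go so far. What remains is an unresolved statement about which codes the data hold.

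**The F33 gap may be harmless.** Full code lists are not shown and validated lists are promised; depression and anxiety are also captured separately from primary care Read codes under Outcome 4; and patients with F33 often may have a listed code too. The second and third of these limit the harm. The first does not remove it, because the explicit list is what the plan fixes, and the cited Read code lists belong to Outcome 4.

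**Stronger readings that the article does not support.**

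- *A stated loss of precision.* A reader might assume that F33 makes up 10% to 30% of intended patients and, from 1/sqrt(1 - s), quote intervals 5% to 20% wider (1/sqrt(0.90) = 1.05; 1/sqrt(0.70) = 1.20). No such share is in the document, and the sum assumes that none of these patients has another listed code.
- *A failure to capture suicide.* The list holds no external-cause codes, but its label is anxiety and depression. The Power calculations section places self-harm and suicide in the previous analyses and turns to commoner outcomes, such deaths still count in all-cause mortality, and the text does not say whether only the underlying cause or any mentioned cause is used.
- *A conflict over the third cause of death.* The abstract names only "all-cause mortality and death due to diseases of the respiratory system and cardiovascular disease". An abstract condenses, and its silence on a third cause is not a decision to drop it.

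**Conclusion.** The point holds on two counts. The main one is the omission of F33: as written, the anxiety and depression outcome is narrower than its label for admissions and for deaths, and events coded only to F33 are misclassified as non-events. Its size is unknown. It rests on two assumptions: that the printed list is the one to be applied, and that recurrent depression is meant to be in scope, which the label and the inclusion of single and bipolar depressive episodes suggest.

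The lesser count is the ICD version. It is a real contradiction that bears on all three cause-specific death outcomes and on no admission outcome, and it is probably a single wrong word. No figure stated in the article changes on either count.

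**What to change.** 1. Add F33 to the anxiety and depression list under both Outcome 2 and Outcome 3. If its exclusion was intended, say so, give the reason, and narrow the label to match.
2. In Outcome 3, name one ICD version that matches the death records received. If some causes of death really are held in ICD-9, give the equivalent codes beside the ICD-10 ranges.

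Both are edits to text and code lists, best made before the outcomes are extracted. The price of the first is a slightly broader outcome, less directly comparable with the earlier count of 213 patients if that count used the present list; running the present list as a sensitivity analysis would keep the link. The second costs nothing beyond checking the data specification, unless a mapping proves necessary.

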##### Outcome 4: Incident respiratory illness, myocardial infarction, depression or anxiety

We will define the adverse event outcomes using the diagnosis records from the Clinical and Referral files in the CPRD. These files record all the diagnoses that the GPs input into their computer system. Each record in the table is given a diagnosis code based on the Read code categorisation. We will use validated Read code lists, for the three adverse event outcomes, respiratory illnesses, myocardial infarction or depression and anxiety, please see the cited papers for Read code lists.^23–25^ For eligible patients we will extract all records from the Clinical and Referral Tables that indicate the patient either received a specific diagnosis or were referred for a specific diagnosis. As with the therapy records for prescriptions described above, each Clinical and Referral Record indicates the date the information was inputted into the system. We will use this date to define the date that the diagnosis was performed. We will define a set of outcomes within 3, 6, 9, 12, 24 and 48 months after first prescription.

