### Statistical analysis

For investigating the effects of varenicline use on each outcome (long-term smoking cessation, frequency of GP and hospital attendance, all-cause and cause-specific mortality, primary care diagnosis of respiratory illness, myocardial infarction, depression or anxiety), we will report a conventional multivariable-adjusted Cox regression, propensity score regression and instrumental variable analysis.

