#### Analysis 1: Conventional cox regression

In our first analysis, a conventional observational analysis, we will estimate HRs of the outcomes using Cox-proportional hazards models and the actual prescriptions issued to the patients.^29^ Each patient's date of entry into the cohort will be the date they were first prescribed a smoking cessation therapy. The date of exit for each outcome will be the date on which they first have an event, or are censored due to end of follow-up or death or leaving the practice. We will report these associations adjusted for basic confounders (age and gender), and results adjusted for all measured covariates described above.

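### The study aims promise incident illness from GP, hospital and death records, but no outcome combines them: Outcome 4 is GP-only, so an infarction known only from HES or ONS is never counted as one

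*Protocol article*

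**What the plan says.** In the Protocol article, Study aims, the question about deaths carries this sentence: "We will investigate the incidence illnesses in the Clinical Practice Research Database (CPRD) using primary care diagnoses, admission to secondary care using ICD-10 codes", together with "Office of National Statistics (ONS) mortality records to maximise the number of events detected". The next question, on physical and mental health conditions, names no data source.

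Outcome 4 defines incident respiratory illness, myocardial infarction, and depression or anxiety: "We will define the adverse event outcomes using the diagnosis records from the Clinical and Referral files in the CPRD". It describes those files thus: "These files record all the diagnoses that the GPs input into their computer system". The Abstract (Methods) has the same scope, "a primary care diagnosis of respiratory illness, myocardial infarction or depression and anxiety", and so does the Statistical analysis section, "primary care diagnosis of respiratory illness, myocardial infarction, depression or anxiety".

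In Analysis 1, patients leave the Cox model at a first event or when they "are censored due to end of follow-up or death or leaving the practice". The Follow-up section also censors at death, and Analysis 2 reuses the entry and exit rules of Analysis 1.

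**The concern.** The aims describe incident illness as drawn from three sources so that few events are missed. The outcome definition uses one. Cardiovascular harm is among the safety concerns that the Introduction gives as motivation, and myocardial infarction is the one specific cardiac diagnosis that the study analyses. If an infarction leads to admission or death and no GP code is entered, it is absent from that analysis. Where the patient dies, the record is censored at the event itself. An effect on infarction that lay mainly in such cases would be weakened or missed in Outcome 4. It would be visible only within a much wider cardiovascular group elsewhere.

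**Working it through.** **Step 1: which source feeds which outcome.**

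| Section | Source | What it defines |
|---|---|---|
| Study aims, mortality question | GP, ICD-10 admissions and ONS | incident illnesses |
| Study aims, physical and mental health question | none named | – |
| Outcome 2 | HES | admissions, including J00-J99 and I00-I52 |
| Outcome 3 | ONS | deaths, including J00-J99 and I00-I52 |
| Outcome 4 | GP Clinical and Referral files | incident respiratory illness, infarction, depression or anxiety |

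Each source is used somewhere. No outcome pools them.

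**Step 2: follow a patient in a linked practice whose infarction has no GP code.**

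- Admitted and survives: counted in Outcome 2 as an I00-I52 admission. In Outcome 4 the patient stays at risk with no event.
- Dies of it: counted in Outcome 3 as an all-cause and an I00-I52 death. In the Outcome 4 Cox models the patient is censored on the date of death, so is event-free up to that date and not for the whole follow-up.
- Instrumental variable analysis: Analysis 3 classes adverse events as occurring or not within windows from 3 to 48 months and does not say how a death inside a window is coded. Treating such a patient as a non-event is an inference.

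In none of these is the case counted as a myocardial infarction.

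**Step 3: what the loss would do.** The protocol states no figure for Outcome 4, so there is none to reproduce. The share s of true infarctions with no GP code is also not given; 10% to 40% is assumed for illustration.

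If s is equal in both groups, the HR is about unchanged. The risk difference is multiplied by (1 − s), with missed cases coded as non-events. The SE of the log HR is multiplied by 1/√(1 − s).

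| s | Risk difference factor | SE factor |
|---|---|---|
| 10% | 0.90 | 1.05 |
| 20% | 0.80 | 1.12 |
| 30% | 0.70 | 1.20 |
| 40% | 0.60 | 1.29 |

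If s differs by group, for a rare event, observed HR ≈ true HR × (1 − s on varenicline)/(1 − s on NRT). With a true HR of 1.0:

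- 20% missed on varenicline and 30% on NRT: 0.80/0.70 = 1.14.
- 30% missed on varenicline and 20% on NRT: 0.70/0.80 = 0.88.

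A harm confined to the missed cases is a special case of this. Suppose 30% of infarctions on NRT are fatal and uncoded, with HR 1.5 for these and 1.0 for the rest. The all-infarction HR is 0.3 × 1.5 + 0.7 × 1.0 = 1.15, while the GP-only analysis would show 1.0.

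**Step 4: what a three-source analysis would cost in precision.** Outcome 2 says causes of hospitalisation are available for about half the sample; the same coverage is assumed here for ONS. Take full capture in the full sample as 1. Full capture in half the sample has an SE factor of 1/√0.5 = 1.41. GP-only in the full sample has 1.05 to 1.29 over the assumed range. The three-source analysis is therefore the less precise of the two unless GP files miss more than half of all infarctions.

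**The case against.** The case for leaving the definition alone is substantial, and most of it stands.

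- **Placement.** The three-source sentence sits under the mortality question. It can be read as a list of sources across the study, since each one does feed an outcome. The Abstract, Outcome 4 and the Statistical analysis section all give a primary care definition. A reader might infer that the plan contradicts itself about how Outcome 4 is defined, and the documents do not support that. What remains is that the sentence speaks of incident illness and of maximising events, and no outcome carries this out.
- **Events analysed elsewhere.** A reader might infer that the most serious infarctions are lost to the study. They are not: they fall in the I00-I52 admissions and deaths of Outcomes 2 and 3. They are only never identified as infarctions.
- **Quality of GP data.** A reader might infer that the protocol itself concedes that GP-recorded infarction is unreliable. The remarks in Data collection and linkage concern hospital care and mortality, and do not name infarction diagnoses.
- **Bias.** A reader might infer that the HR will be biased. Equal under-recording leaves it about unchanged, and no document gives a reason for recording to differ by drug. The earlier adjusted mortality HR of 0.49 in Power calculations shows that death rates differed between the groups. It does not show that the share of infarctions lacking a GP code differs.
- **Condensed article.** A fuller approved protocol exists and may hold supplementary definitions. That does not remove the mismatch within this text.

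**Conclusion.** The point holds in a limited form. The aims describe a three-source search for incident illness that no outcome section implements. As written, an infarction recorded only in HES or ONS is not counted as an infarction anywhere, and the same definition applies to incident respiratory illness. The GP-only definition is used consistently and is not shown to be a wrong main definition.

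The size cannot be found from the documents. Over an assumed missed share of 10% to 40%, equal in both groups, the loss is an SE 5% to 29% larger and a risk difference cut to 0.90 to 0.60 of its true value. Bias in the HR needs unequal under-recording. The values 1.14 and 0.88 show what a ten-point difference in missed share (20% against 30%) would do and are not estimates. This is a cheap improvement that serves the protocol's own stated purpose. It is not a fault that undermines the study.

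**What to change.** 1. Reconcile the sentence under the mortality question in Study aims with the Abstract, Outcome 4 and the Statistical analysis section.
2. Keep the full-sample Outcome 4 analysis and label it as GP-recorded illness.
3. Add a supplementary analysis in linked practices. For myocardial infarction and for respiratory illness, take the earliest of a GP code, a HES admission with a relevant ICD-10 code, or an ONS death from that illness.
4. In that analysis, count death from the outcome illness as an event and not as censoring, both in the Cox models and in the fixed-window instrumental variable analysis.

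The cost is ICD-10 code lists for the two illnesses and one further run on linked data that the study already uses. The downside is wider CIs, because linked data cover about half the sample; this is acceptable because the GP-recorded analysis stays. Tabulating the events found only in HES or ONS by treatment group would also supply the missed share that is now unknown.

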### Inclusion and exclusion criteria

We will include patients who were older than 18 and were prescribed medicines in British National Formulary (BNF) category 4.10.2 (Nicotine Dependence) from 1 September 2006, when varenicline was introduced to the UK, to the present. We will use patients prescribed other smoking cessation products (nicotine patches, gum, lozenges, and inhalers) as controls for patients prescribed varenicline. We will include patients whose records were classified as ‘acceptable’ by the CPRD from all ‘up to standard’ general practices (GPs) at least 18 months prior to date of entry of each cohort (1st March 2005). Up to standard GPs are practices that have submitted data that meets the CPRD quality control thresholds. Patient data are defined as ‘acceptable’ by the CPRD if they meet minimum quality control standards, for example their registration period with their GP is valid.

We will exclude patients who registered at a GP less than 365 days before the first recorded prescription, to allow for high-quality assessment of baseline data and possible confounders. Patients prescribed bupropion in the year before their index prescription of varenicline or nicotine replacement therapy will be excluded from the analysis. In the primary analysis we will exclude patients initially prescribed nicotine replacement therapies and varenicline together, although in our previous analysis this only occurred for 0.25% of all prescriptions.^13^

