#### Confounding factors

We will include gender, age in years at time of first prescription, previous psychiatric illness/consultation, previous use of psychotropic medications such as hypnotics, antipsychotics and antidepressants, previous self-harm, measures of alcohol consumption where appropriate mean/median number of GP visits per year, body mass index, SEP (deprivation score for area or residence) and major chronic illness (including: diabetes, cancer, arthritis) using the Charlson index.^26^
^27^ Relevant Read codes will be identified either by validated code lists or by searching for each of these events in the Read code dictionaries to identify any missing Read codes. Collider bias is a potential threat to the analysis; this type of bias occurs when the association between two variables changes on conditioning of a third variable if the third variable is affected by the first two variables. Collider bias could occur if we conditioned on events that happened as a result of the prescription the patient was issued. To prevent this bias from affecting our results, we will define each covariate using data inputted prior to the first prescription.^28^ If there are missing data in the covariates we will consider using multiple imputation.

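### Outcome 4 is called incident, but its stated rule also admits re-coded or late-entered old disease, which dilutes and can bias the estimate

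*Protocol article*

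**What the plan says.** The section heading in the protocol article reads "Outcome 4: Incident respiratory illness, myocardial infarction, depression or anxiety". The text below it fixes the record source, the code lists, the extraction rule, the date rule and the windows:

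- **Records:** for eligible patients the plan is to "extract all records from the Clinical and Referral Tables that indicate the patient either received a specific diagnosis or were referred" for the condition.
- **Date:** "each Clinical and Referral Record indicates the date the information was inputted into the system", and then "We will use this date to define the date that the diagnosis was performed".
- **Windows:** "We will define a set of outcomes within 3, 6, 9, 12, 24 and 48 months after first prescription".

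The related sections are:

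- **Analysis 1:** "The date of exit for each outcome will be the date on which they first have an event", with entry at the first prescription. Follow-up likewise ends at an event or at censoring.
- **Inclusion and exclusion criteria:** "We will exclude patients who registered at a GP less than 365 days before the first recorded prescription". The stated reason is good baseline and confounder data. The other exclusions concern bupropion and joint prescribing.
- **Exposure measures:** a 12-month period without use is required for the drugs. There is no counterpart for the outcome conditions.
- **Confounding factors:** "previous psychiatric illness/consultation, previous use of psychotropic medications such as hypnotics, antipsychotics and antidepressants, previous self-harm", plus alcohol, GP visits per year, body mass index, deprivation and chronic illness through the Charlson index. Covariates use only data entered before the first prescription.

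**The concern.** An incident outcome needs a population at risk of a first event. Under the stated rule, a patient with long-standing respiratory illness or depression stays in the cohort. A review, a referral or a repeat code after the index date then satisfies the definition.

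The date rule opens a second route. A diagnosis made before the prescription but typed in afterwards is absent from the baseline covariates and is counted as a post-index event.

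The article calls these its adverse event outcomes and intends to send findings to regulators. If many events are old disease, a real effect on new disease is harder to see. If the arms also differ in prior disease after adjustment, part of that difference appears as a treatment effect.

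**Working it through.** **Does any section restore incidence?** The heading asks for new disease. The extraction rule takes all diagnosis or referral records. The eligibility criteria do not mention prior outcome disease. Analysis 1 counts the first event after cohort entry, which stops repeat records in follow-up from being counted several times but does not make the event first-ever. Psychiatric history appears as a covariate, which implies that such patients remain in the cohort. So nothing restores it.

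**Which way might the arms differ?** The only indication is in Power calculations. The age- and sex-adjusted hazard ratios for varenicline versus nicotine replacement move towards 1 on fuller adjustment: self-harm or suicide 0.73 to 0.90, all-cause mortality 0.43 to 0.49. This suggests that higher-risk patients receive nicotine replacement. It is not a prevalence of any Outcome 4 condition.

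**Is there a plan figure to reproduce?** None for Outcome 4. The projected interval breadths elsewhere do reproduce: 0.56/√1.7 = 0.43, 0.21/√1.7 = 0.16, and 8.0/√(182/110) = 6.2. They do not bear on this point. The two-year event counts are hospital admissions and are not split by arm or by prior disease.

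**Illustration; every input is assumed.** Let p be the prevalence of the condition before index, i the risk of new disease in those free of it, and r the chance that a prior case is coded again in the window. Then

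P(any record) = (1 − p)·i + p·r.

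*True null for new disease, no covariate adjustment.* Example with p = 20% (nicotine replacement) and 15% (varenicline), i = 2%, r = 30%:

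- varenicline: 0.85 × 0.02 + 0.15 × 0.30 = 0.062
- nicotine replacement: 0.80 × 0.02 + 0.20 × 0.30 = 0.076
- ratio: 0.062/0.076 = 0.816

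| p, NRT / varenicline | i 2%, r 10% | i 2%, r 30% | i 5%, r 30% | i 5%, r 50% |
|---|---|---|---|---|
| 10% / 10% | 1.000 | 1.000 | 1.000 | 1.000 |
| 10% / 7% | 0.914 | 0.825 | 0.900 | 0.858 |
| 20% / 15% | 0.889 | 0.816 | 0.875 | 0.839 |
| 30% / 20% | 0.818 | 0.731 | 0.800 | 0.757 |
| 40% / 30% | 0.846 | 0.788 | 0.833 | 0.804 |

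Restricting to patients free of the condition returns 1.00 by construction.

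*True risk ratio 1.30 for new disease, equal prevalence, no drug effect on re-coding.* Example with p = 20%, i = 2%, r = 30%: (0.80 × 0.02 × 1.3 + 0.06)/(0.80 × 0.02 + 0.06) = 0.0808/0.0760 = 1.063.

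| p, both arms | i 2%, r 30% | i 5%, r 30% | i 5%, r 50% |
|---|---|---|---|
| 10% | 1.113 | 1.180 | 1.142 |
| 20% | 1.063 | 1.120 | 1.086 |
| 30% | 1.040 | 1.084 | 1.057 |

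The dilution is milder on the risk-difference scale of the instrumental variable analysis. There the contrast is (1 − p)·i·0.3 instead of i·0.3, a factor of 1 − p, or 0.7 to 0.9 for p of 30% to 10%.

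**The case against.** **Extraction is not definition.** Pulling all records could be a data step, since earlier records are needed to tell new disease from old, and the heading may state the real target. A condensed article may leave a wash-out rule to the full protocol. This has some force, but the section goes on to give the date rule and the windows. Anyone following it as written would count old disease, so this is more than a missing detail.

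**Adjustment is broader than psychiatric history and comorbidity.** Psychotropic use, self-harm and GP visit frequency are also listed, and visit frequency bears on how often disease is re-coded. The chronic illness list is not exhaustive. This stands and should reduce imbalance. But prior respiratory illness and prior myocardial infarction are not named, a summed index is not condition-specific history, and adjustment does not make a re-coded case new.

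**The instrumental variable analysis.** If its assumptions hold, imbalance in prior disease creates no false effect. That also stands, but the outcome would still mix old and new disease. The Cox and propensity analyses share covariates and outcome, so their agreement would not be reassuring.

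**The dating.** The section likens these dates to those of therapy records, which Exposure measures describes as dates of issue. The entry wording may therefore be loose. No entry lag is given, and no separate event date for GP records is mentioned.

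**Recurrence is a legitimate safety event.** True, and for that reason prior-disease patients should be reported separately, not dropped.

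**A stronger reading.** A reader might infer that varenicline will falsely appear protective. The document does not support that. A false effect requires prevalence or re-coding to differ between arms after adjustment, no prevalence by arm is given, and the hazard ratios quoted concern death and self-harm.

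**Conclusion.** The label and the definition of Outcome 4 contradict each other. As written, re-coded or late-entered old disease can count as an event. Two consequences follow:

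- **Dilution** of an effect on new disease needs no imbalance between arms, only that the drug does not act equally on re-coding. In the illustration 1.30 becomes 1.04 to 1.18.
- **Bias** arises only if prior disease or its re-coding differs between arms after adjustment. The direction would plausibly favour varenicline. Under a true null the unadjusted illustration gives 0.73 to 0.91 with unequal prevalence and 1.00 with equal prevalence.

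These ranges rest wholly on assumed prevalence, incidence and re-coding. They show what size is possible and do not predict the bias of this study, which cannot be derived from the document.

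**What to change.** 1. For each Outcome 4 condition, analyse as incident the first record after index among patients with no pre-index record of that condition.
2. Report patients with prior disease as a separate recurrence stratum. If they are instead kept in one analysis, rename the outcome *any recorded diagnosis* and add history of that specific condition to the Cox and propensity models.
3. Date outcomes by the clinical event date where the record holds one, so that a pre-index diagnosis entered late is not counted as a post-index event.
4. Keep the rule that covariates use only data entered before the first prescription. Re-dating them by event date could admit history typed in after treatment began, which is the collider problem that rule guards against.

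The cost is mostly wording, because pre-index records are already needed for the covariates. The real price is fewer patients and events per condition in the incident analysis, and so wider intervals there.
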